## Abstract

**Background:**

Burns are a painful and traumatic experience, particularly in children. Reduced pain and anxiety positively influences re-epithelialisation rates in paediatric burn patients, however current literature fails to fully explain the effects of pain and anxiety and their links with wound healing. This study will determine if Burnaid® hydrogel dressing is an effective treatment for reducing pain in the acute period of a burn injury. It is hypothesised that a reduction in pain will then improve re-epithelialisation time in comparison to plastic wrap, which is standard practice at our institution — a metropolitan tertiary paediatric hospital located in Brisbane, Australia.

**Methods/design:**

A randomised controlled trial will be conducted to assess the effectiveness of Burnaid® as an analgesic adjunct to cold running water first aid for the treatment of paediatric burns. Participants will include children aged between 0 and 16 years with an acute thermal burn injury (total burn surface area < 20%) presenting to the Department of Emergency within 24 h of the burn occurring. Participants will be randomised into one of two groups: (1) Burnaid® hydrogel (intervention arm) or (2) plastic wrap (control arm). Participants will also be stratified into one of two groups based on factors that influence pain intensity: (1) high pain risk or (2) low pain risk. High pain risk factors include foot burns, hot coal/ash/fire pit burns, burn area greater than 5%, and circumferential burns. The primary outcome is the intervention’s effect on reducing acute pain. Secondary outcomes include days to re-epithelialisation, pulse rate, temperature, salivary cortisol and α-amylase, anxiety, and cost-effectiveness. Sample size calculations have shown that 36 participants will be recruited into each group.

**Discussion:**

This study will provide comprehensive data on the analgesic properties of Burnaid® as an adjunct to first aid for the treatment of acute paediatric thermal burns. If the intervention is effective in reducing pain, Burnaid® will be integrated as standard practice within the hospital’s Department of Emergency. This study replicates a real-world scenario in order to identify clinically significant analgesic and wound-healing effects.

**Trial registration:**

Australian New Zealand Clinical Trials Registry, ACTRN12617001274369. Prospectively registered on 5 Sept 2017.

**Electronic supplementary material:**

The online version of this article (10.1186/s13063-018-3057-x) contains supplementary material, which is available to authorized users.

## Background

Paediatric burn injuries pose a major epidemiological problem worldwide, with one-fourth of all burn injuries occurring in children under the age of 16, the majority of whom are under 5 years of age [1]. Comprehensive management of burn wounds includes a challenging spectrum of acute, chronic, traumatic and surgical wounds with a wide range of anatomical locations and depths. Improving acute paediatric burn management is critical because untreated pain is thought to contribute to long-term sensory issues such as chronic pain, paraesthesia, dysesthesia and psychological conditions [2]. Moreover, optimal pain management may have significant implications with respect to re-epithelialisation rates in children with burn injuries [3].

Historically, burn injuries have been viewed as one of the most severe forms of trauma, and burn pain is considered one of the most severe forms of acute pain [4, 5]. Burn treatment is also associated with significant pain and distress, and current standard treatments for such injuries have been insufficient in providing the analgesic needs for paediatric patients [6–9]. Paediatric burn patients undergo multiple painful and distressing procedures during their wound care and rehabilitation, which can cause severe long-term physiological and emotional effects [2]. If acute pain is not adequately managed, it can lead to altered long-term pain perception and maladaptive coping strategies, which can persist into adulthood [10–13]. Previous research also suggests that inadequate pain control can lead to the development of anticipatory anxiety for future medical procedures [9]. It is estimated that 10–20% of young patients who have sustained a burn injury go on to develop psychological disorders such as post-traumatic stress disorder [13, 14]. Therefore, optimising pain management during the acute phase of a paediatric burn is critical not only for the physical and cosmetic outcome of the injury but also for the child’s well-being at the time and in the long term.

### First aid

Correct first aid in the acute phase of a burn is essential for preventing further tissue damage, reducing pain in the acute phase and improving time to re-epithelialisation [15–20]. Immediate cooling via the use of cold running water (CRW) between 2 °C and 15 °C for 20 min (applied within 3 h of the initial injury) is the recommended gold standard first aid for thermal burns, according to the Australian and New Zealand Burn Association [15, 17, 21, 22]. After adequate CRW the burn must be covered to protect the wound, reduce pain and prevent hypothermia [8]. The use of a hydrogel dressing that aids in cooling and hydration to the burn wound could be an ideal adjunct to current first aid practice. Advanced wound-dressing technologies require clinical data to support their use, and currently there is limited empirical evidence to support the use of hydrogel dressings as an analgesic adjunct to first aid for the treatment of acute burn injuries. Moreover, there are no studies investigating the use of these dressings in the paediatric burn population.

### Use of hydrogels on burns

Current guidelines recommend burn wound covering after CRW first aid [8]. Acute burn wound coverings are required to be transparent and non-adherent and to have high application and removal ease. Plastic wrap fulfils these criteria and, excluding applications to the face, is a practical choice of dressing for acute burn injuries. In comparison to plastic wrap, Burnaid® hydrogel dressings (Mundicare, Sydney, Australia) may provide additional pain relief via an evaporative cooling effect and may thereby assist in wound healing [23–25]; however, empirical evidence is still limited. The Burnaid® hydrogel dressing comprises a 3-mm-thick, sterile, open foam polyester urethane pad that is impregnated with a propylene glycol gel which contains more than 90% purified water. Following the recognised standard of first aid treatment for acute burn injuries, Burnaid® is recognised as an adjunct to first aid whose aim is to reduce pain. Moist interactive wound dressings provide pain relief via an evaporative cooling effect and create a moist environment which soothes exposed nerve endings in the skin [26]. Hydrogel dressings provide a concomitant cooling and wound-covering function and dissipate heat from the burn wound, and dressings come in a wide range of sizes which can be applied to all areas of the body [23, 27, 28].

The use of hydrogel dressings as an acute treatment for burn injuries has increased in the pre-hospital setting over the past decade. Allison showed that 39% of emergency medical services (EMS) in the United Kingdom applied hydrogel dressings (e.g., Water-Jel, Water-Jel Technologies, Carlstadt, NJ, USA; Burnshield, Levtrade, Johannesburg, South Africa) during patient transport to hospital for burn injuries [29]. Walker and colleagues showed that 76% of UK fire and rescue services applied hydrogel dressings to cover burns, whereas 23% used plastic wrap as a burn wound dressing until EMS arrived [30]. Moreover, Cuttle and colleagues conducted an audit of first aid interventions for paediatric burn patients presenting to a tertiary burns centre located in Brisbane, Australia. This investigation found that Burnaid® hydrogel dressings were applied by ambulance services in 12.9% of cases [31]. In addition, authors of a 2013 retrospective investigation reported that 5% of paediatric burns patients who presented to a tertiary burns centre in Sydney, Australia, had Burnaid® hydrogel dressings applied as a first aid dressing [32]. A large retrospective investigation into pre-hospital paediatric burn care was conducted in 2014 using data from electronic ambulance response forms for patients aged between 0 and 5 years who were attended by the Queensland Ambulance Service from 2008 to 2010 [18]. Data were collected from 117 paediatric burn incidents occurring within the Brisbane, Townsville and Cairns regions. Burnaid® was the most commonly used dressing during patient transport and was applied to 55.6% of all paediatric burn patients. Brisbane paramedics applied Burnaid® dressings in 44.3% of paediatric burn cases, whereas ambulance services in North and Far North Queensland applied Burnaid® during patient transport in 72.7% and 60.9% of cases, respectively [18]. The difference in rates of use between regions further exemplifies the need for evidence-based guidelines for the use of hydrogel dressings in burn patients.

In a clinical investigation in which researchers evaluated the efficacy of hydrogel dressings in burn wound care, it was reported that hydrogel dressings conform well to the wound bed, are quick and easy to apply, and allow for wound inspection through the dressing [33]. In addition, it was observed that hydrogel dressings are effective for providing hydration to deep partial thickness burns and act to absorb exudate without becoming adherent to the wound bed. It was further reported that hydrogel sheet dressings are well tolerated by patients, who report no pain associated with dressing changes or between dressing changes [33]. The researchers in that study also commented on the paucity of evidence for the use of hydrogel dressings in burn care and their use in major burn wounds. This demonstrates the need for further investigation into the efficacy of hydrogel dressings for the acute treatment of burn injuries, so that evidence-based guidelines regarding their use and application can be developed. The potential that hydrogel dressings can reduce pain during the acute burn phase should not be underestimated in a clinical area where pain is most probably at its greatest. The primary aim of the present research is to assess the analgesic properties of Burnaid® hydrogel dressings as an adjunct to current first aid in comparison to plastic wrap, which is currently used to cover burn injuries following CRW.

### Effect of pain and inflammatory mediators on wound healing

The association between pain and wound healing is complex. In patients with significant tissue damage such as a burn, there is a prolonged and intense release of inflammatory mediators, and this can result in a state of hyperexcitability, which leads to an increased perception of pain [34]. It is evident that prolonged pain, such as that experienced by patients with significant burn injuries, can have maladaptive effects on wound healing time [35] and individual pain thresholds [2]. Prolonged release of inflammatory mediators from injured tissue acts to sensitise the inflamed area to pain via lowering the excitation threshold of nociceptors [34, 36]. This lowering of activation threshold (hyperalgesia) results in the perception of pain from typically non-painful stimuli and is often the case in burn patients who report increasing pain even where good progressive wound healing has occurred [36]. This further demonstrates the critical need to optimise pain management during the acute phase of a paediatric burn.

### Distraction, pain and wound healing

Several studies describe the relationship between decreased pain and improved re-epithelialisation rates in paediatric burn patients [3, 6, 37, 38]. A recent randomised controlled trial assessed the effectiveness of a procedural preparation and distraction device (Ditto™; Diversionary Therapy Technologies, Toowong, Australia) in reducing pain in paediatric burn patients during burn wound care [3]. This trial found that children who received the procedural preparation and distraction treatment reported significantly lower procedural pain scores (measured using the Wong-Baker Faces Pain Rating Scale) in comparison to patients who received standard care during their burn wound treatment (*p* ≤ 0.05). Parent and caregiver observational reports of procedural pain were also found to be lower in patients who received the preparation and distraction device (*p* < 0.001). Furthermore, children who received the Ditto™ device re-epithelialised an average of 2.1 days faster than children in the standard care group (CI, − 4.38, 0.10; *p* = 0.061). Although not statistically significant, this result was clinically significant because the 2-day improvement rate in re-epithelialisation in patients who received the Ditto™ treatment translated into a sizeable reduction in the need for scar monitoring: 26% of patients in the Ditto™ treatment group re-epithelialised beyond 14 days, in contrast to 48% of participants in the standard practice group.

### Objectives

The objective of the present study is to compare the effectiveness of plastic wrap (currently used to cover burns following CRW at Lady Cilento Children’s Hospital (LCCH; Brisbane) and Burnaid® hydrogel dressing to reduce pain intensity in children who have sustained a burn injury prior to the application of a standard burns dressing.

### Hypotheses

It is hypothesised that Burnaid® is more effective than plastic wrap at reducing pain intensity in the acute burn phase. It is also hypothesised that decreased pain experienced during the acute phase of the burn injury will speed up wound healing time and will result in a clinically significant reduction in days to full re-epithelialisation after application in children after a burn.

## Methods/design

### Design

A single-centre, superiority, two-arm, parallel-group randomised controlled trial will be conducted to examine the effectiveness of Burnaid® hydrogel dressing as an analgesic adjunct to first aid in comparison to plastic wrap. The present study includes methods that have been modelled on successful prior trials conducted by members of this investigative team at the same participating facility as the present trial [39, 40]. The Consolidated Standards of Reporting Trials guidelines for randomised controlled trials will be followed, and the protocol adheres to the Standard Protocol Items: Recommendations for Interventional Trials guidelines (SPIRIT; *see* checklist in Additional file 1). Ethics approval for this project was obtained from LCCH and The University of Queensland human research ethics committees (HRECs). A flow diagram of the trial is provided in Fig. 1.

**Fig. 1 Fig1:**
[figure not shown]
Data collection flow diagram

### Setting

Recruitment will be conducted in the Department of Emergency (DEM) and Pegg Leditschke Children’s Burns Centre Outpatient Department (OPD), located at LCCH, Brisbane. LCCH is categorised as a level 6 service, providing tertiary-level care for the state’s most critically and seriously injured children.

### Inclusion criteria

Children recruited into the study will be aged between 0 and 16 years and will have acquired an acute thermal burn injury that is < 20% of the total body surface area (TBSA). The child must present to the DEM or burns OPD within 24 h of sustaining the injury and must have no silver dressing application prior to this admission.

### Exclusion criteria

Exclusion criteria for mechanism of injury are chemical, electrical, inhalation or friction burns; children who do not arrive within 24 h of sustaining their acute burn injury; children who do not receive appropriate first aid treatment; children who received prior treatment of a silver dressing or ointment; children who are non-English-speaking; children with cognitive impairments; children who are ventilated or require initial wound care in theatre for debridement or grafting; current involvement with the Department of Communities (child safety); children with known sensitivity to hydrogels or hypersensitivity; and children who have co-morbidities that would potentially impair would healing (e.g., diabetes) or that may exacerbate itch and pain.

### Recruitment

Treating physicians/nursing staff of all children meeting the inclusion/exclusion criteria and presenting to the LCCH, Brisbane, will determine eligibility for enrolment in the study. Medical staff, once establishing the child’s eligibility, will then notify the parents/guardians and child of their eligibility to participant in the study. With parent/caregiver permission an investigator aligned with the study will discuss the trial with the parent/caregiver, seek informed consent from the parent/caregiver, and seek assent from the child (when appropriate). This trial will use a stratified sampling method taking into account factors which influence pain intensity in paediatric burn patients, based on anecdotal evidence and observations from paediatric burns surgeons and the unit’s experience (unpublished hospital data audit). Once informed consent is obtained participants will be stratified into one of two groups: (1) high pain risk or (2) low pain risk. Participants presenting to LCCH DEM or burns OPD with one or more of the following criteria will be placed into the high pain risk group:Foot burns (unilateral or bilateral)Hot coal/ash/fire pit burnsCircumferential burnsTBSA > 5%

All other participants who meet the inclusion criteria for the trial but do not present with one or more of the four aforementioned pain risks will be placed in the low pain risk group. Following stratification, children will be randomised to one of the two treatment groups. Randomisation will be undertaken using a computerised random number sequence-generating programme, and treatment allocation will be masked by the use of sealed, opaque, identical, serially numbered envelopes prepared by an independent party. The researchers will not be blinded to which group the child is in, because they will be collecting set measures throughout the acute burn period. At any point throughout the study period the parent/guardian or child can withdraw from the study without any implications for the child’s burn care, and all withdrawals and discontinuations will be recorded.

### Treatments

#### Intervention

Burnaid® hydrogel dressing will serve as the treatment intervention in this trial. Paediatric burn patients randomised to the intervention arm will have the hydrogel dressing applied following 20 min of CRW, and the dressing will remain on the burn for a minimum of 20 min. Burnaid® will be applied as per the manufacturer’s instructions, followed by standard burn care, typically consisting of wound cleaning, debridement and silver dressing application.

#### Control

Plastic wrap is the current acute wound covering applied to thermal burn injuries at LCCH, and it will serve as the control arm in this trial. Participants randomised to receive plastic wrap will have the dressing applied after first aid and will have the dressing remain on for a minimum of 20 min, followed by standard burn care.

### Data collection

Information regarding patient demographics and clinical details will be obtained from the parent/guardian, child (where age appropriate), and patient chart to record mechanism of injury, affected area, burn TBSA, what first aid was provided, form of transport, and time to presentation (*see* SPIRIT figure in Fig. 2). Apart from which type of dressing the child is receiving prior to the application of silver dressings, all participants will receive the standard medical care as would those not in the trial.

**Fig. 2 Fig2:**
[figure not shown]
SPIRIT figure. SPIRIT schedule of study recruitment, intervention and assessments. Allocation to the intervention group will occur in the Department of Emergency at Lady Cilento Children’s Hospital upon patient admission following a thermal burn injury; t1 = 3–5 days after burn injury and each subsequent dressing change; t2 = 3 months after burn injury; t3 = 6 months after burn injury

Following patient enrolment and randomisation, acute measures will be collected in LCCH DEM. Acute measures will include pain (measured using the Faces Pain Scale–Revised [FPS-R]; Face, Legs, Activity, Cry, Consolability scale [FLACC]; and visual analogue scale [VAS]), pulse rate, temperature, respiratory rate, and salivary cortisol and α-amylase, which will be recorded by the primary investigator. Acute measures will be collected before and after the application of the randomised dressing and before and after silver dressing application from the child, parent/guardian, and nursing staff. In addition, peak FLACC scores during wound cleaning and debridement will be documented, as will all analgesia and distraction techniques. All participants will have their burn wounds photographed using 3D imaging after wound debridement in the DEM to assess burn area. Patients (where appropriate) and parents/caregivers will be sent home with a diary to record pain scores and medications required prior to their first change of dressing (COD), which will typically occur 3 days after injury. Participants and parents/caregivers will be asked to bring this home diary with them to their first dressing change in the burns OPD.

Data collection in the burns OPD will continue through to the child’s treating clinician classifying the burn wound as 95% re-epithelialised. Measures collected in the burns OPD at each dressing change appointment will include pain (measured using FPS-R, FLACC, and VAS), pulse rate, temperature, respiratory rate, and salivary cortisol and α-amylase at each dressing change appointment. These measures will be collected before and after silver dressing removal and before and after the application of new silver dressings (*see* Fig. 4). Anxiety and itch will also be assessed at each COD appointment. At the first COD appointment, all participants will have their burn wound scanned using a non-invasive treatment referred to as laser Doppler imaging to measure burn depth and vascularity of the affected area. In addition, all participants will have a 3D image of their burn taken at each COD to assess the area of the wound and its rate of re-epithelialisation.

Following wound re-epithelialisation and discharge from the burns OPD, scar outcome will be assessed at 3 and 6 months post-burn for all participants. At each 3- and 6-month follow-up, patients will have their burn wounds scanned using ultrasound to assess scar thickness; 3D imaging to assess scar area; DSM ColorMeter (Cortex Technology, Hadsund, Denmark) to examine scar colour and pigmentation; and Patient and Observer Scar Assessment Scale (POSAS), Brisbane Burn Scar Impact Profile (BBSIP) and Child Health Utility 9D Index (CHU9D) to measure health-related quality of life. Thy will also undergo itch assessment, and saliva samples will be collected to examine baseline cortisol and α-amylase levels.

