#### Blinding

Owing to the nature of the trial, blinding will not be possible, because treating clinicians, nursing staff, patients and their families will be aware of the intervention. The primary investigator will be present when the acute wound dressings are being applied and removed to obtain pain scores and additional measures from the participant, caregiver and nursing staff. The acute wound covering applied to each participant cannot be masked within this environment, and therefore investigator blinding will not be possible. In order to incorporate an element of blinding in the trial, an expert panel of burn wound specialist will conduct a blinded review of 3D photographs for all participants to assess burn wound depth and re-epithelialisation at each dressing change until complete wound healing. Wherever possible during data collection analysis, treatment groups will be de-identified.

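### Pain before the dressing is scored after randomisation by unblinded raters, so acute-pain analyses that use this baseline (but not an unadjusted primary comparison) are open to influence from the allocation

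*Protocol article*

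**What the plan says.** The Recruitment section gives the order as consent, then stratification by pain risk, then randomisation: "Following stratification, children will be randomised to one of the two treatment groups". Concealment up to assignment is by envelope: "treatment allocation will be masked by the use of sealed, opaque, identical, serially numbered envelopes prepared by an independent party".

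The Data collection section (text after Fig. 2) continues: "Following patient enrolment and randomisation, acute measures will be collected in LCCH DEM". It then sets out when these measures are taken: "Acute measures will be collected before and after the application of the randomised dressing and before and after silver dressing application". They comprise FPS-R, FLACC and VAS pain scores, pulse rate, temperature, respiratory rate and saliva markers. No section places a pain score before randomisation.

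On awareness of the allocation, Recruitment says "The researchers will not be blinded to which group the child is in, because they will be collecting set measures throughout the acute burn period", and the Blinding section says "blinding will not be possible, because treating clinicians, nursing staff, patients and their families will be aware of the intervention". The one blinded assessment is the panel review of 3D photographs, which does not cover pain.

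The primary outcome is the nurse-rated FLACC once the acute dressing is on (Measure 2 in Fig. 3). Data analysis plans regression models for between-group differences without naming covariates, mixed models for repeated measures, tests of group differences at baseline, and analyses of change over time within groups.

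**The concern.** A baseline score is a safe covariate, or a safe starting point for a change score, because the allocation cannot have affected it. That protection comes from the order of events. Here the stated order puts the first pain score after randomisation, and the people who supply it (nurse, parent and, where old enough, child) belong to groups that the protocol says are aware of the intervention.

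The Ancillary pain measures section itself describes FLACC as capturing distress as well as pain. A rater's expectation, or a family's reaction to the allocation, could move such a score differently in the two arms. Any analysis that subtracts the baseline or adjusts for it would carry that difference into the estimated treatment effect. A comparison of baseline pain between arms would no longer describe the groups as randomised.

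**Working it through.** **Sequence.** Setting the sections side by side:

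1. Recruitment: consent, stratification, randomisation.
2. Data collection: acute measures follow enrolment and randomisation.
3. Data collection and Fig. 3 caption: the first acute measure comes after cold running water and before the randomised dressing.
4. Recruitment and Blinding: researchers, nursing staff, patients and families are unblinded.

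The pre-dressing score therefore falls after randomisation, and nothing in the text keeps its raters unaware of the arm.

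**The plan's own figures.** Inputs from Sample size: difference 1.8, SD 2.4, power 0.8, type I error 0.05 (taken as two-sided). The normal approximation is 2 × (1.960 + 0.842)² × 2.4² / 1.8² = 27.9, so 28 per arm. The two-sample t-test gives 28.9, so 29 per arm with power 0.801. This agrees with the stated 29. The calculation concerns the score after the dressing and does not depend on the baseline.

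**Illustration of what a contaminated baseline does.** The following are assumptions, not figures from the protocol:

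- a shift b in the mean baseline of one arm relative to the other;
- a before-after correlation rho of 0.3 to 0.7;
- equal SDs before and after, so that the adjustment slope equals rho;
- no true effect, and no shift in the score after the dressing.

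Absolute bias by analysis:

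- unadjusted comparison of the score after the dressing: 0;
- change score: b;
- baseline-adjusted regression: rho × b.

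| Assumed b | Change-score bias (share of 1.8) | Adjusted bias, rho 0.3 to 0.7 (share of 1.8) |
|---|---|---|
| 0.25 | 0.25 (14%) | 0.075 to 0.175 (4% to 10%) |
| 0.5 | 0.50 (28%) | 0.15 to 0.35 (8% to 19%) |
| 1.0 | 1.00 (56%) | 0.30 to 0.70 (17% to 39%) |

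For b = 0.5 the bias can be set against the standard error with 29 per arm. The unadjusted SE is 2.4 × √(2/29) = 0.630. The adjusted SE is 0.630 × √(1 − rho²), and the change-score SE is 0.630 × √(2(1 − rho)). With δ = bias/SE, the false-positive rate is Φ(δ − 1.96) + Φ(−δ − 1.96). Over rho 0.3 to 0.7 this gives 0.057 to 0.122 for the adjusted analysis and 0.103 to 0.176 for the change score, against a nominal 0.05.

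**The case against.** Five points can be made on the other side.

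- **The primary outcome does not use the baseline.** It is the score after the dressing, the sample size is built on that score, and no change-from-baseline endpoint is specified. Covariates are commonly left to the statistical analysis plan. This stands. A reader might infer that the primary comparison is biased by the order of measurement, but the document does not support that for an unadjusted comparison.
- **The moment of envelope opening is not stated.** The reasons given under Blinding concern a dressing that can be seen, which establishes awareness from application onward. Figs. 1 to 3 are not available in the text reviewed. It is therefore an inference that each rater already knows the arm at the first score. It is a reasonable one, since the measures are placed after randomisation and no safeguard is described.
- **Size and sign are unsupported.** A reader might take a half-point bias in favour of Burnaid® from the illustration. The document gives no basis for the 0.5 or for its direction. Relief at being allocated the new dressing would lower its baseline and bias a change score against it. If the same expectation also moved the later score by c, the change-score bias would be c − b, and the two could partly cancel.
- **Not every measure is equally exposed.** Infants do not react to an allocation, and temperature is hardly open to a rater's expectation. This also stands. The observer-rated scores are the main exposure.
- **The larger threat is elsewhere.** Unblinded nurses score the primary outcome itself, and the protocol acknowledges that this cannot be avoided. Re-timing the baseline leaves that untouched.

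What remains is that the stated order gives up the protection of a pre-randomisation baseline, and that protection costs almost nothing to keep.

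**Conclusion.** The point holds in a limited form. On the text, the baseline acute measures are taken after randomisation with unblinded raters, and may be influenced by knowledge of the allocation. This is a risk, not a demonstrated bias. It bears on any comparison of baseline pain, on before-to-after or repeated-measures analyses of acute pain, and on any regression that adjusts for baseline pain. It does not bear on an unadjusted comparison of FLACC after the dressing.

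The direction is unknown. The size depends wholly on the assumed shift: for b = 0.5, 0.5 points in a change score or 0.15 to 0.35 points after adjustment, against a target of 1.8. These figures show how the bias scales; they do not estimate it.

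**What to change.** State in Data collection that the first pain scores and vital signs (those taken before the dressing, presumably Measure 1 in Fig. 3) are recorded after consent and stratification and before the allocation envelope is opened. Log the clock time of that measurement and of envelope opening on the data collection form. If this is already the practice, the sentence placing all acute measures after randomisation should be corrected to say so.

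No extra staff, procedures or participants are needed. The requirement of 29 per arm and the target of 72 are unchanged. The only downside is that the envelope is opened a few minutes later, for the time that the first measurement already takes.
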